### Primary Outcome: IOP

The study’s primary outcome is assessing IOP (mm Hg) before and after the intervention. All participants will undergo ophthalmologic examinations on the same day. A slit lamp examination will first be performed on all eyes, followed by IOP measurement in the sitting position, using an iCare IC100 rebound tonometer (iCare Finland Oy) [19]. The instrument will be calibrated regularly according to the manufacturer’s instructions. A disposable, single-use probe was loaded into the device and aligned 4 to 8 mm perpendicular to the central cornea. Six consecutive measurements were performed. The software automatically discarded the highest and lowest values, and the IOP was calculated from the remaining 4 values. Only proper measurements (indicated by a green background within acceptable limits) were included.

### Secondary Outcomes

#### Best Corrected Visual Acuity

Best corrected visual acuity, reported in logarithm of the minimum angle of resolution units, will be measured using a standardized visual acuity chart under controlled lighting conditions to assess any changes due to ocular massage [10,20]. Baseline and postintervention measurements will be recorded to determine the impact on visual function.

#### SC Area and SC Diameter

SC area (μm^2^) and SC diameter (μm) will be analyzed using anterior segment optical coherence tomography (AS-OCT) [11,23]. High-resolution images of the temporal corneoscleral region will be captured at baseline and after the intervention, ensuring consistency in scanning alignment. SC area will be delineated manually using ImageJ software, while SC diameter will be measured from the anterior to posterior endpoints of the canal [12,24].

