**Objective:**

This study aims to examine the impact of digital and EyePeace ocular massage on IOP fluctuations and investigate whether the observed reduction in IOP is attributable to morphological changes in the Schlemm canal (SC).

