#### Mobile App–Based Quality of Vision Questionnaire

The original Quality of Vision Questionnaire includes 10 visual symptoms, measured in terms of frequency, severity, and impact on daily activities. It was designed to assess patients’ subjective visual experience, especially after refractive or cataract surgery [26]. In this study, participants will complete the Quality of Vision Questionnaire [26] before and after ocular massage to assess subjective visual disturbances, visual clarity, and visual discomfort. The questionnaire will be delivered via a web application on the WeChat platform (Tencent Holdings Ltd) [27]. An independent examiner will perform all measurements to minimize bias, and data will be analyzed for statistical significance using appropriate paired comparison tests. In addition to the Quality of Vision Questionnaire, 3 items will be administered to measure overall quality of vision score (Likert scale, 0-10), ocular pain score (Likert scale, 0-10), and ocular discomfort score (Likert scale, 0-10; Multimedia Appendix 1).

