### Allocation

The patients will be randomly assigned to 1 of 3 groups: digital ocular massage (group A), EyePeace ocular massage (group B), or no ocular massage (group C). Randomization will be performed by a statistician using a network-based randomization procedure with a fixed block size of 4 to ensure balanced group allocation. Group assignments will be placed in sealed, opaque envelopes held by the PI. Each envelope will include the participant’s information and intervention assignment.

This trial will use a single-masked design. Participants will be aware of their assigned intervention (digital ocular massage, EyePeace ocular massage, or no ocular massage). However, the data analysis team and clinical assessment staff will remain masked to group allocation. All clinical assessments will be performed by a masked examiner who is not involved in data collection or group allocation. The conditions and protocols for disclosure of group information, if required, will be established and overseen by the PI.

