### Statistical Methods

Following the guidelines for statistical analysis plans in clinical trials [18,29], all statistical analyses will be conducted using SPSS software (version 25.0; IBM Corp). The significance level is set at 5% (2-tailed), with a 95% CI. The normality of data distribution will be assessed using the Shapiro-Wilk test. Data will be compared using 2-way repeated measures analysis of variance. If the hypothesis is unmet (*P*>.05), the Greenhouse-Geisser correction will be applied. Multiple comparisons will be made between groups at different time points using the Bonferroni-Holm correction. If the Shapiro-Wilk test indicates that the data are not normally distributed (*P*<.05), nonparametric tests will be used: paired comparisons will use the Wilcoxon signed-rank test, and between-group comparisons will use the Kruskal-Wallis H test. Statistical significance will be considered at *P*<.05 for 2-tailed tests unless otherwise specified. To ensure participant safety, the distribution of AEs will be described for both digital ocular massage and EyePeace ocular massage groups. The incidence rates of AEs were compared using the chi-square test or the Fisher exact test, as appropriate. An intention-to-treat analysis will be the primary analytic approach. All participants will be included in the analysis based on their original allocation, regardless of protocol adherence. For missing data, multiple imputation will be performed using the fully conditional specification method, assuming data are missing at random. A sensitivity analysis using a per-protocol approach will also be conducted to compare results. Given the short duration of this study, an interim analysis will not be performed.

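### Schlemm canal and trabecular meshwork images are read with masking to group but not to time point, which leaves the before/after tests, though not the between-arm contrast, open to reader expectation

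*Protocol article*

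**What the plan says.** Under SC Area and SC Diameter, the protocol article states that "High-resolution images of the temporal corneoscleral region will be captured at baseline and after the intervention, ensuring consistency in scanning alignment" and that "SC area will be delineated manually using ImageJ software". SC diameter is a distance between the two ends of the canal. The next subsection takes TM width and thickness from AS-OCT images as distances between anatomical landmarks. Table 1 schedules all four measures at baseline and at follow-up.

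Masking is described under Allocation: "the data analysis team and clinical assessment staff will remain masked to group allocation". The same paragraph adds that "All clinical assessments will be performed by a masked examiner who is not involved in data collection or group allocation". The questionnaire subsection contains one more general safeguard: "An independent examiner will perform all measurements to minimize bias, and data will be analyzed for statistical significance using appropriate paired comparison tests". None of these sentences mentions time point, image coding or reading order.

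Under Statistical Methods, the main analysis is given as "Data will be compared using 2-way repeated measures analysis of variance", followed by Holm-corrected comparisons between groups at each time point. If normality is rejected, "paired comparisons will use the Wilcoxon signed-rank test" and the Kruskal-Wallis test compares the groups.

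**The concern.** Placing a canal border by hand is a judgement, and the study is built on the expectation that massage changes the canal. The abstract's objective asks whether the fall in IOP can be attributed to SC changes, and the Objectives section speaks of a possible correlation. A reader who can tell the baseline image from the later one has a reason, conscious or not, to draw the later canal differently.

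Masking to group does not remove that cue. It makes the shift the same in every arm, which protects comparisons between arms but not comparisons of after with before. A significant within-arm change in SC area could then be reported as an anatomical effect of massage when it came from the tracing.

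**Working it through.** **What can be taken from the document.** It gives no SD, expected change or repeatability for any SC or TM measure. The only sample size calculation is for IOP, and it is used here only for the arm size. It reproduces: with 3 groups, SD 1.9 and means equally spaced at 0, 1 and 2 mm Hg, the noncentrality is 24 × (1² + 0² + 1²) / 1.9² = 48 / 3.61 = 13.30. Power is then 90.2% at 24 eyes per group (88.8% at 23), counting each eye as independent. The 24 eyes come from 12 participants per arm, so both 24 and 12 independent units are shown below.

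**Step 1: one within-arm before/after test.** Assume no true change and a reader who adds a constant shift of *d* SDs of the within-eye change to every post-intervention reading. The paired t statistic is noncentral t with n − 1 degrees of freedom and noncentrality *d*√n. The two-sided 5% critical values are 2.069 (n = 24) and 2.201 (n = 12).

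| Assumed shift *d* | *d*√24 | Rejects, n = 24 | *d*√12 | Rejects, n = 12 |
|---|---|---|---|---|
| 0 | 0 | 5.0% | 0 | 5.0% |
| 0.2 | 0.98 | 15.6% | 0.69 | 9.7% |
| 0.3 | 1.47 | 29.1% | 1.04 | 15.8% |
| 0.5 | 2.45 | 65.0% | 1.73 | 35.3% |

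The t-test stands in for the Wilcoxon test here, so the rates are illustrative.

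**Step 2: the planned tests together.** This is a simulation of 20,000 trials with three arms, no true change and the same shift in every arm:

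| Units per arm | Shift | Group-by-time | Time effect | Either massage arm, within-arm | Massage arm significant, control not |
|---|---|---|---|---|---|
| 24 | 0 | 5.0% | 5.2% | 9.6% | 9.1% |
| 24 | 0.25 | 5.0% | 55.4% | 39.0% | 30.4% |
| 24 | 0.5 | 4.8% | 98.6% | 87.3% | 30.2% |
| 12 | 0.25 | 4.9% | 31.0% | 23.7% | 20.7% |
| 12 | 0.5 | 5.1% | 83.7% | 58.4% | 38.0% |

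The group-by-time test keeps its level at every shift. The time effect and the within-arm tests do not. The last column shows that setting separate within-arm results side by side does not make proper use of the control arm. That pattern appears in about 30% of trials at shifts of 0.25 to 0.5 SD with 24 units, against about 9% with no shift. It is not monotone: at 0.8 SD with 24 units it falls to 3.4%, because the control arm then also turns significant.

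**Step 3: the other between-arm tests.** A constant added to every post-intervention value leaves differences between arms at that time point unchanged, and it leaves the ranks used by Kruskal-Wallis unchanged. These tests are protected on the same condition as the group-by-time test.

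**The case against.** The strongest reply is that the design already deals with this bias. The no-massage group is imaged at both time points, the main method is a two-way repeated measures ANOVA, and its follow-up comparisons are between groups. The Wilcoxon test is only the fallback for non-normal data, and the sentence on paired tests sits in the questionnaire subsection, so applying it to SC readings is an inference. All of this stands, and it confines the point to within-arm tests and the time effect. Likewise, a shift equal for every eye would leave the correlation between SC change and IOP change unaltered.

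A second reply is that the article never says the reader knows the time point, and that a fuller imaging procedure may exist. The first half is right, so the point is conditional. The second half carries less weight: the article gives masking its own paragraph and names what is masked, and that is group allocation.

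A reader might also infer that the between-arm SC comparison is compromised because the image reader could learn the arm from staff who delivered or supervised the massage. The document gives no support for that; its stated intent is that assessors stay masked to group.

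**Conclusion.** The point holds in a limited form. As written, the masking does not protect before/after SC and TM readings from a reader who knows the time point. The exposed results are the within-arm tests (the Wilcoxon fallback) and the ANOVA time effect. Under the assumed shifts of 0.2 to 0.5 SD, the false-positive rate of one within-arm test rises from 5% to between 16% and 65% with 24 independent eyes, or between 10% and 35% with 12 independent units. These figures assume a constant shift and no true change; the document does not allow the shift to be estimated, and its actual size could be zero.

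The conclusion does not extend to the between-arm SC comparison while the group mask holds, nor to IOP, which is read by a rebound tonometer that computes the value itself. It would also be too strong to say that the mechanistic objective fails: the damage arises if that objective is argued from within-arm canal changes. This is an inexpensive improvement to the secondary outcomes, not a flaw in the primary analysis.

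**What to change.** Extend the masking statement under Allocation so that AS-OCT reading is masked to time point as well as group. In practice:

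- Strip arm, date and time labels from every image and assign random codes.
- Have the existing reader measure baseline and post-intervention images in one shuffled batch.
- Link codes to visits only after all SC and TM readings are locked.
- State that the SC and TM conclusions rest on the group-by-time contrast with the no-massage arm, and treat within-arm changes as descriptive.

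The abstract reports data collection as complete, so tracing may already be done. In that case the retained images can be re-read this way; the article does not state that images are kept, so this needs confirming. If both eyes of the 50 recruited participants were imaged once at each time point, that is 50 × 2 × 2 = 200 images.

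No participant, visit or additional reader is needed, and the sample size does not change. The cost is some file coding or a re-read. The downside is that the two images of an eye can no longer be viewed side by side, so alignment must be secured at capture, which the imaging subsection already requires.

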#### TM Width and TM Thickness

TM parameters, including width (μm) and thickness (μm), will be assessed from AS-OCT images [13]. TM width will be defined as the distance between the scleral spur and the Schwalbe line, whereas TM thickness will be measured at the anterior endpoint and midpoint of the SC [14,25].

#### Mobile App–Based Quality of Vision Questionnaire

The original Quality of Vision Questionnaire includes 10 visual symptoms, measured in terms of frequency, severity, and impact on daily activities. It was designed to assess patients’ subjective visual experience, especially after refractive or cataract surgery [26]. In this study, participants will complete the Quality of Vision Questionnaire [26] before and after ocular massage to assess subjective visual disturbances, visual clarity, and visual discomfort. The questionnaire will be delivered via a web application on the WeChat platform (Tencent Holdings Ltd) [27]. An independent examiner will perform all measurements to minimize bias, and data will be analyzed for statistical significance using appropriate paired comparison tests. In addition to the Quality of Vision Questionnaire, 3 items will be administered to measure overall quality of vision score (Likert scale, 0-10), ocular pain score (Likert scale, 0-10), and ocular discomfort score (Likert scale, 0-10; Multimedia Appendix 1).

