### Interventions

Eligible participants will be randomly assigned in a 1:1:1 ratio to (1) digital ocular massage (group A), (2) EyePeace ocular massage (group B), or (3) no ocular massage (group C). Group A and group B participants will receive ocular massage for 10 minutes [5,10,11]. Any participant experiencing an adverse event (AE) will be withdrawn from the trial, documented, provided appropriate treatment, and referred immediately to the principal investigator (PI). Clinical research staff will receive professional training covering participant enrollment, treatment procedures (including risks and benefits), and data collection processes. Participants will be sufficiently informed about the study and provided with compliance education to enhance participation and minimize noncompliance. Study staff will proactively contact participants in advance by telephone or SMS text message. EyePeace is a flexible, medical-grade silicone device designed to apply gentle, pulsatile vertical pressure to the closed eyelids. Although it does not contain a built-in pressure gauge, manufacturer specifications suggest that the applied force typically ranges from 0.2 to 0.5 N. To ensure consistency, all participants in the EyePeace ocular massage group received standardized instructions and a demonstration before use. In addition, a trained examiner supervised the massage procedure to ensure correct technique and duration. For the digital ocular massage group, clinical staff applied consistent fingertip pressure guided by prior training and feedback from pilot sessions, aiming to replicate the mechanical effect of the EyePeace ocular massage device. Although exact biomechanical equivalence between digital ocular massage and EyePeace ocular massage cannot be assured, the standardization procedures were designed to ensure comparability in massage duration, eyelid area coverage, and application frequency.

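### The only test named for the Quality of Vision Questionnaire is a paired pre-post test, which does not use the randomised no-massage arm and is not reconciled with the general analysis plan

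*Protocol article*

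**What the plan says.** The protocol article deals with the analysis of the questionnaire in two places.

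- **Mobile App–Based Quality of Vision Questionnaire (Secondary Outcomes).** The design is pre-post: "participants will complete the Quality of Vision Questionnaire [26] before and after ocular massage". The analysis sentence reads: "data will be analyzed for statistical significance using appropriate paired comparison tests". No between-arm contrast is given there. The 0-10 items follow that sentence and have no test attached: "In addition to the Quality of Vision Questionnaire, 3 items will be administered to measure overall quality of vision score" and, in the same list, ocular pain and ocular discomfort.
- **Statistical Methods.** The general plan is: "Data will be compared using 2-way repeated measures analysis of variance". It adds: "Multiple comparisons will be made between groups at different time points using the Bonferroni-Holm correction". If the data are non-normal, "paired comparisons will use the Wilcoxon signed-rank test, and between-group comparisons will use the Kruskal-Wallis H test". The questionnaire is neither mentioned nor excluded. The section does not say which ANOVA term carries the massage effect, or whether Kruskal-Wallis is run on change or on post-intervention values.

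The trial randomises 1:1:1 with a no-massage group, and Table 1 schedules the questionnaire at baseline and follow-up in all three arms. The control data needed for a between-arm comparison will therefore exist.

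**The concern.** The question is whether massage disturbs vision. The null of a paired test in a massage arm is that the mean (or median) change over the session is zero. That is the same as no massage effect only if nothing else moves the scores.

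Other influences are credible here. Under Primary Outcome, every participant has a slit lamp examination and tonometry. Table 1 repeats IOP, OCT-based measures and the questionnaire at follow-up in all arms. Under Allocation, participants know which intervention they received. A shift in self-reported scores could therefore occur in every arm, and a paired test cannot separate it from massage.

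The Abstract makes this questionnaire the means of monitoring adverse effects on quality of vision, so it bears on the tolerability conclusion. Within-arm tests also invite a second misreading: significance in one arm and not in another taken as a difference between arms.

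**Working it through.** **The plan's own figure.** The documents give no power or error figure for the questionnaire. The sample size concerns IOP only. It reproduces: with means 0, 1, 2 and SD 1.9, f = √(2/3)/1.9 = 0.43, noncentrality = 24 × 2/1.9² = 13.3, and power is 90.2% at 24 eyes per group. It does not bear on this point.

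**Inputs.**
- Participants per arm: 36/3 = 12 (Study Design). Participants, not eyes, complete the questionnaire.
- Two-sided 5% level (Statistical Methods).
- Shared session shift d, in SDs of the change score, equal in all three arms, with no massage effect. This is an **assumption**; the documents give neither a shift nor an SD for these scores.

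**Step 1: rejection by a paired test in one massage arm.** For a paired t test, the statistic is noncentral t with 11 df and noncentrality d√12. The rejection probability is P(|T| > 2.201). At d = 0.5 the noncentrality is 0.5 × 3.464 = 1.73 and the probability is 35%. At d = 0.2, 0.3 and 0.8 it is 10%, 16% and 71%.

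**Step 2: the plan's nonparametric version.** Simulation of the Wilcoxon signed-rank test against Kruskal-Wallis on change (1,500 trials per setting, normal change scores, 12 per arm):

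| Shared shift (SD of change) | Wilcoxon, one massage arm | Kruskal-Wallis on change, three arms |
|---|---|---|
| 0 | 5.2% | 4.9% |
| 0.25 | 12.7% | 4.8% |
| 0.5 | 34.8% | 5.4% |
| 0.75 | 65.2% | 6.1% |

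The simulation standard error at 5% is √(0.05 × 0.95/1500) = 0.6 points, so the last column is compatible with 5%. A further check with exact Wilcoxon p-values (6,000 trials) gave slightly lower rates in one massage arm: about 4%, 11%, 31% and 61%. The pattern is the same.

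**Step 3: the between-arm alternative.** With two time points, the group by time test equals a one-way ANOVA on change. Over 20,000 trials at d = 0, 0.5 and 0.8 it rejected 4.9% to 5.1% of the time.

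**Step 4: does comparing significance across arms repair it?** No. With independent arms and paired t tests at d = 0.5, at least one of the two massage arms is significant with probability 1 − (1 − 0.353)² = 58%. Significance in a massage arm but not in control has probability 0.581 × 0.647 = 38%. Part of this is ordinary multiplicity: at d = 0 the same two figures are 10% and 9%.

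**Step 5: do the two sections together fix the right test?** The ANOVA contains a group by time term, but that term is not named as decisive. The Holm comparisons are between groups at each time point, so they are not stated as comparisons of change. Bounded symptom scores in healthy volunteers may well fail the Shapiro-Wilk test. The fallback then has Wilcoxon for pre-post change within arms, and a Kruskal-Wallis test that is not stated to use change. On that branch, the only test explicitly tied to change is the paired one.

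**The case against.** The strongest reply is that Statistical Methods already supplies between-arm analysis for the data in general and does not exclude the questionnaire. The paired sentence can then be read as the paired part of that plan, and the group by time term is the test requested here. The reading is possible, and it is why this point concerns an unreconciled sentence and not a fixed invalid analysis. It does not settle the matter: the outcome-specific sentence names only paired tests, and the general section leaves the decisive contrast unnamed.

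Other points on that side stand:

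- A reader might infer that any change shared with control will be declared a massage effect. The document gives no such decision rule, nor does it call the paired test primary for these scores.
- A reader might extend the paired sentence to pain and discomfort. Those items come after it with no test of their own, so this is an interpretation. The sentence's scope is also loose, since it speaks of an examiner performing measurements, which fits a self-completed questionnaire poorly.
- Error rates computed on 24 eyes per arm would be higher, but nothing says that the questionnaire is scored by eye, so they do not apply.
- The inflation depends entirely on the assumed shift.

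It may also be said that a condensed article leaves test detail to an analysis plan. That would cover silence, but here the article names a type of test.

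**Conclusion.** The point holds as a conflict between two sections with a specific risk attached. The questionnaire subsection names only a within-arm test, and the general plan does not make clear that the between-arm difference in change decides whether massage has an effect.

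If the paired sentence governs, false significance in a given massage arm is about 13%, 35% or 65% at an assumed shared shift of 0.25, 0.5 or 0.75 SD with 12 participants per arm. With no shift it is about 5%, and a between-arm test of change stays at about 5% whatever the shift. These rates assume roughly normal change scores and an equal shift in all arms.

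The outcome is secondary and the IOP analysis is not touched. The change is worth making because it is small and the control data will already have been collected.

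**What to change.** In the questionnaire subsection, replace the reference to paired tests with a statement along these lines: the effect of massage on the questionnaire score, and on each of the three 0-10 items, is tested at participant level by the between-arm difference in change from baseline. The method can be the group by time term, a baseline-adjusted model or, for skewed scores, Kruskal-Wallis followed by Mann-Whitney on change. Compare each massage arm with no massage, and EyePeace with digital massage, using the Holm correction already planned and 95% CIs. Report within-arm paired results as descriptive only.

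In Statistical Methods, name the same contrast as the test of a massage effect, and state that Kruskal-Wallis is applied to change, so that the two sections agree.

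The cost is a few words and no new data. Between-arm intervals will be wider than within-arm ones. The change does not remove reporting bias, because participants know their arm; that limitation should be stated beside the results.
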